### Quality control of the research

To avoid bias and ensure patients’ medical adherence, we follow the standards in the subsequent text:

Self-monitoring of blood pressure: According to the recommendation of China’s guideline for hypertension (2018) (16), we will use the home blood pressure monitoring method to monitor patients’ blood pressure monthly. All patients will receive training for blood pressure measurements from professional cardiologists at enrollment and every 3 months. We will evaluate pre-enrollment medication adherence and include only patients with good adherence. We will require all patients to measure the blood pressure of the left brachial artery twice at least 1 min apart in the morning before breakfast and taking antihypertensive medications, and after urination and defecation. Before blood pressure measurement, all patients will be required to rest for at least 5 min. Blood pressure is measured using the YUYUE electronic sphygmomanometer (YE660A, China). Researchers will collect blood pressure data once a month.Protocol-noncompliance: If the patient’s SBP does not reach the assigned target during follow-up, the cardiologists will evaluate the patient according to the predefined antihypertensive treatment algorithm (Figures 2, 3).Unable to complete the required CTA examinations: We will contact each patient one month before the CTA examination by telephone to ensure completion. If patients are unable to complete CTA examinations in the required time interval, they will not be included in the final analysis.

### Safety monitoring

Each participating investigator has primary responsibility for the safety of the individual participants under his/her care. At each follow-up, CRC will specifically query participants for adverse events (AE) and serious adverse event (SAE) and recorded them in the case report form (CRF). Event Adjudication Committee members are responsible to make final ascertain of safety outcomes.

In our current study, adverse event (AE) is defined as any intervention related unfavorable medical outcomes, including any clinically obvious symptom, abnormal sign, or disease. In our current study, we will monitor AE including hypotension, dizziness, angioedema, headache.

Adverse event is considered as serious adverse event (SAE) only when it met following criteria: fatal or life-threatening, result in significant or persistent disability, or require hospitalization or surgical intervention, including:

Symptomatic hypotension.Arrhythmia.Acute kidney failure.Electrolyte abnormalities.Injurious falls.Syncope.Unexpected events for which the investigator believes that intervention caused the event or contributed to the immediate cause of the event.

### Statistical analysis

#### Sample size

The sample size is estimated using the PASS 15 (PASS Corporation, United States). In our preliminary studies, the 2-year instability events risk was approximately 20.7% in UIA patients with hypertension and 11.5% in UIA patients with controlled hypertension (17). In this study, we assume that EBPL could decrease the risk of aneurysm rupture and growth by 50%. At *α* = 0.05, *β* = 0.90, we need to enroll 506 patients (253patients in the SBPL group and 253 patients in EBPL group). By estimating the clinical dropout rate at 10%, the required sample size was calculated to be 282 patients in each group. This study prepared to include 570 patients in both groups (285 in each group), which could meet the statistical requirements.

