#### Step 2: Randomization and intervention

Enrolled UIA patients will be randomized at a ratio of 1:1 to the EBPL group and SBPL group after obtaining informed consent. Dynamic randomization using the minimization method is used as the randomization of subjects to the EBPL or SBPL group. Randomization and enrollment of subjects are made using the online randomization system. Randomization factors are as follows: age at the time of obtaining the informed consent (≥ 60 years or < 60 years), sex (female or male), aneurysm location [Anterior Communicating Artery (Acom)/Anterior Cerebral Artery (ACA), Internal Carotid Artery (ICA), Middle Cerebral Artery (MCA) and Posterior circulation (PC)]. Patients in the EBPL group are required to keep systolic blood pressure at <120 mmHg and those in the SBPL group at 120-140 mmHg.

This study aims to compare the effects of different blood pressure targets rather than specific medications. Therefore, the blood pressure treatment protocol is flexible in terms of the choice and doses of antihypertensive medications, but there should be preferences based on cardiovascular outcome trials results and current guidelines [such as thiazide diuretic, Calcium Channel Blockers (CCBs), Angiotensin-Converting Enzyme Inhibitors (ACEIs), and Angiotensin II Receptor Blockers (ARBs)]. If adopting another dose frequencies is not required (e.g., twice a day), the preference will be choosing long-acting antihypertensive agents, i.e., once per day.

The cardiologists may select among the available study antihypertensive medications for initiation of therapy. Other drugs not supplied by the trial may also be used as the cardiologists determines appropriate. However, all antihypertensive regimens should include one or more drug classes with strong cardiovascular outcome data from large randomized controlled hypertension trials. If three drugs are needed, a thiazide-type diuretic, a RAS blocker (ACEI or ARB, but usually not both), and CCB make a very effective and usually well-tolerated regimen. The decision is left to the investigator as long as the BP goals are achieved.

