#### Endpoint and outcome evaluation

Before locking the database for analysis, we intend to test its plausibility and effectiveness. We will exclude the cases that could influence the accuracy of the conclusion. Patients who do not meet the requirement of quality control may be further excluded based on the consensus of the investigators’ discussion.

Categorical variables are presented as numbers (no.) and percentages (%). Continuous variables with normal distribution are expressed as means and standard deviation, and medians and inter-quartile range (IQR) if otherwise. The differences between groups in continuous variables are compared by performing the student’s t-tests or Wilcoxon rank sum tests, and the differences in categorical variables are compared using the chi-square tests or Fisher’s exact tests. The incident rate (IR) of PR and its 95% confidence interval (CI) are calculated. The univariate and multivariate Cox regression analyses are performed in PR-related analysis. The result of Cox regression analysis is presented as hazard ratio (HR) and 95% CI. SPSS 24.0 (SPSS, Chicago, IL) is used for statistical analysis, and bilateral *p* < 0.05 is considered statistically significant.

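### The 90% power holds only if the SBPL arm, although treated to 120–140 mmHg, carries the 20.7% risk at the top of the plan's own range; at 11.5% it is about 64%

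*Protocol article*

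**What the plan says.** The Sample size section gives two risks from preliminary work: "the 2-year instability events risk was approximately 20.7% in UIA patients with hypertension and 11.5% in UIA patients with controlled hypertension". On the effect it says "we assume that EBPL could decrease the risk of aneurysm rupture and growth by 50" per cent. The result follows: "At *α* = 0.05, *β* = 0.90, we need to enroll 506 patients", which is 253 per arm. The value printed as β can only be meant as power. Allowing for 10% dropout gives 282 per arm, and 285 per arm (570 in all) are planned. The section does not say which risk is given to SBPL.

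On the arms, Step 2 says that EBPL patients "are required to keep systolic blood pressure at <120 mmHg and those in the SBPL group" at 120–140 mmHg. Visits are monthly in both groups. Step 3 adds milepost visits every six months in both groups, at which treatment is to be stepped up when systolic pressure is above target. Good adherence is an entry criterion.

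The Abstract states a different basis: 85% power for a 60% reduction, with no control risk given.

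**The concern.** The power of a two-arm comparison of event risks depends heavily on the control risk. The plan quotes two, one nearly twice the other, and its sample size matches the higher. The arm that would carry this higher risk is itself managed to a pressure target, with regular review and escalation. If its patients behave more like the controlled group in the plan's own data, there will be fewer events than planned and less power than stated.

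What is at stake is how a null result is read. A reader who believes the trial had 90% power to detect a halving of risk would take a non-significant result as fairly strong evidence against such an effect. At power nearer two thirds, it would not be.

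**Working it through.** **Inputs.** From Sample size: risks of 20.7% and 11.5%, 50% reduction, power 0.90, 253 per arm, 10% dropout, 285 per arm enrolled. From Endpoint and outcome evaluation: two-sided 5% ("bilateral *p* < 0.05 is considered statistically significant"). Evaluable number: 285 × 0.9 = 256.5, taken as 257 per arm.

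**1. Reproducing the plan's figure.** The unpooled two-proportion formula is

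n per arm = (1.960 + 1.282)² × [p1(1−p1) + p2(1−p2)] / (p1−p2)².

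With p1 = 0.207 and p2 = 0.1035: 10.507 × 0.25694 / 0.010712 = 252.03, rounded up to **253**, the plan's figure. The pooled version gives 256. Then 253 / 0.9 = 281.1, rounded up to 282, also as stated.

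**2. Other pairings at 90% power, two-sided 5%.**

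| SBPL vs EBPL | n per arm (unpooled / pooled) |
|---|---|
| 20.7% vs 10.35% | 253 / 256 |
| 20.7% vs 11.5% | 331 / 334 |
| 11.5% vs 5.75% | 496 / 499 |

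So the control risk behind 253 is 20.7%.

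**3. Power at other SBPL risks, keeping the 50% reduction.** With pooled variance under the null,

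power = Φ{ [|p1−p2|√n − 1.960√(2p̄(1−p̄))] / √[p1(1−p1) + p2(1−p2)] }.

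For 11.5% vs 5.75% and n = 257: p̄ = 0.08625, the numerator is 0.0575 × 16.03 − 1.960 × 0.3970 = 0.1437, the denominator is 0.3949, the ratio is 0.364 and Φ = 0.642.

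| SBPL risk | 253 per arm | 257 per arm (10% dropout) | 285 per arm (no dropout) |
|---|---|---|---|
| 11.5% | 63.5% | 64.2% | 68.7% |
| 13% | 69.4% | 70.1% | 74.5% |
| 15% | 76.3% | 76.9% | 81.0% |
| 16.1% (midpoint) | 79.5% | 80.2% | 84.1% |
| 18% | 84.4% | 85.0% | 88.4% |
| 20.7% | 89.8% | 90.2% | 92.9% |

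A log-rank calculation (Schoenfeld, hazard ratio 0.5) at 11.5% gives 63–64% with 253–257 per arm. A continuity-corrected comparison gives 57–58%.

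**4. The Abstract's statement.** A 60% reduction from 20.7% (to 8.28%) has 98.1% power at 257 per arm and 98.9% at 285, not 85%. A 60% reduction from 11.5% (to 4.6%) has 82.2% at 257 and 85.9% at 285. The Abstract and the Sample size section therefore do not share one set of assumptions.

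**The case against.** The strongest reply is that 11.5% is not shown to be the SBPL risk. Controlled hypertension is not defined in the article. It may have meant a stricter level than 120–140 mmHg, or patients selected because control was achieved. SBPL is a target, not a guarantee: patients enter with systolic pressures of 130 to 180 mmHg, and the notes to the SBPL algorithm let the clinician decide not to intensify further. The primary outcome also includes aneurysm-related symptoms, whereas the effect assumption mentions only rupture and growth. If the preliminary risks used a narrower definition, the trial's event risk could be higher. All of this stands. It makes 64% the figure at one end of a range.

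Three stronger readings are tempting, and the documents do not support them.

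- A reader might infer that the true power is 64%. That needs the SBPL risk to be 11.5%, which is not established.
- A reader might infer that the 50% effect is impossible because control against no control yields only 1 − 11.5/20.7 = 44%. The text contrasts patients with hypertension and patients with controlled hypertension. It never describes the first group as uncontrolled, and some may have been treated. The 44% is suggestive at most.
- A reader might infer from the Abstract that the authors really planned on 11.5%. The match at 285 per arm is close, but the Abstract names no control risk, and 20.7% vs 11.5% at 285 per arm also gives 85.0%, for a 44% reduction. The 85% does not identify its source.

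Nor is the sample size miscalculated: the arithmetic is right for its inputs. What is open is the choice of input, which the plan neither states nor justifies. None of the objections restores 90% as a general property of the design.

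**Conclusion.** The point holds in conditional form. The stated 90% is the best case within the plan's own range of risks. Of the two quoted risks, the one for controlled hypertension is the closer description of an arm managed to 120–140 mmHg, and nothing in the article justifies using the other.

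The conclusion rests on four assumptions: the 50% reduction is kept, about 257 per arm are evaluable, the test is two-sided at 5%, and the SBPL risk lies between the two quoted figures. Power of 80% needs an SBPL risk of about 16%. If the risk were 11.5%, 90% power would need 499 evaluable per arm, or 499 / 0.9 = 555 enrolled per arm (1,110 in all) against 570 planned. That figure shows the size of the gap and is not a request to enlarge the trial.

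**What to change.** Keep 570 patients and revise the Sample size section as follows.

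- Name the risk assigned to SBPL and justify it for an arm treated to 120–140 mmHg, including what controlled hypertension meant in the preliminary data.
- Replace the single 90% figure with power over SBPL risks of 11.5–20.7%, at about 257 evaluable per arm: about 64% to 90% for a 50% reduction, and about 82% for a 60% reduction from 11.5%.
- Reconcile this with the Abstract so that both places state the same effect, control risk and power. An 85% figure does not follow from a 60% reduction at 20.7%, which gives about 98%.
- State that a non-significant primary result will be interpreted from the confidence interval, not as evidence of no effect.

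The cost is one reworded paragraph, one sentence in the Abstract and a less favourable power statement. Enrolment, endpoints and treatment do not change.

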#### Endpoint and outcome evaluation

Before locking the database for analysis, we intend to test its plausibility and effectiveness. We will exclude the cases that could influence the accuracy of the conclusion. Patients who do not meet the requirement of quality control may be further excluded based on the consensus of the investigators’ discussion.

Categorical variables are presented as numbers (no.) and percentages (%). Continuous variables with normal distribution are expressed as means and standard deviation, and medians and inter-quartile range (IQR) if otherwise. The differences between groups in continuous variables are compared by performing the student’s t-tests or Wilcoxon rank sum tests, and the differences in categorical variables are compared using the chi-square tests or Fisher’s exact tests. The incident rate (IR) of PR and its 95% confidence interval (CI) are calculated. The univariate and multivariate Cox regression analyses are performed in PR-related analysis. The result of Cox regression analysis is presented as hazard ratio (HR) and 95% CI. SPSS 24.0 (SPSS, Chicago, IL) is used for statistical analysis, and bilateral *p* < 0.05 is considered statistically significant.

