**Methods/design:**

This trial is a multicenter, prospective, open-label, randomized controlled trial with minimization to ensure allocation concealment. Five hundred seventy patients with unruptured intracranial aneurysms and hypertension will be recruited by nine centers in China. Patients will be allocated to the standard blood pressure lowering (SBPL) group (systolic blood pressure at 120–140 mmHg) or the enhanced blood pressure lowering (EBPL) group (systolic blood pressure at <120 mmHg). The primary outcome is aneurysm instability within 24 months after appropriate blood pressure lowering therapy, including aneurysm growth and aneurysm rupture. During follow-up, Blood pressure data will be collected monthly, while radiological examination for aneurysms will be performed at 6 ± 1 months, 12 ± 1 months and 24 ± 1 months. The trial has 85% power to reduce 60% of aneurysm instability.

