### Outcomes and relative definitions

The primary efficacy outcome is UIA instability, including aneurysm growth, rupture or aneurysm-related symptoms during 24-month follow-up. The definitions of UIA instability are listed as follows:

Aneurysm growth is defined as one or more of the following: (1) growth of more than 1 mm in at least one direction, (2) growth of more than 0.5 mm in at least two directions, (3) growth of more than 20% of baseline aneurysm size in any direction, or (4) new appearance of irregularity on the UIA.Aneurysm rupture is diagnosed when patients have the symptoms of non-traumatic subarachnoid hemorrhage (e.g., severe headache and sudden coma) attributable to the target UIA, imaging evidence of hemorrhage on CT or MRI, and/or bloody cerebrospinal fluid from lumbar puncture.Occurrence of aneurysm-related symptoms is diagnosed as sentinel headache (a sudden and severe headache attributable to the UIA within 2 weeks of onset, and without prior history of significant headache within the previous 5 years), oculomotor nerve palsy (a sudden headache with one or several symptoms of pupillary light reflex disappearing, ptosis, or extraocular myoparalysis, ipsilateral to a UIA in the vicinity of the affected oculomotor nerve and without systemic cause such as diabetes), other cranial neuropathy (such as visual field defect secondary to UIA compression of the optic apparatus without alternative cause), or seizure related to UIA inflammation (defined as EEG or clinically determined seizure activity generated from inflammatory changes in the brain parenchyma surrounding the UIA on imaging, and without prior history of seizure or other cause of seizure).

Two investigators who are unaware of the patient’s information assess the occurrence of UIA instability and ischemic brain or cardiac events at 6 months (± 1 month), 12 (± 1 month) months, and 24 (± 1 month) months through monthly follow-up and imaging examinations of UIA.

The primary safety outcome is any ischemic cerebral or cardiac events during 24-month follow-up. This includes one or more of the following: new or more frequent transient ischemic attacks, new clinical or radiological ischemic stroke, angina, new myocardial infarction, or reperfusion therapy for myocardial infarction. Ischemic brain or cardiac events are defined as follows:

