TIA is defined as a transient episode (duration of symptoms < 24 h) of neurological dysfunctions caused by focal brain, spinal cord, or retinal ischemia without showing acute infarction on non-contrasted CT (NCCT).Ischemic stroke is a persistent episode of neurological dysfunctions caused by focal brain, spinal cord, or retinal ischemia, which shows acute hypodense infarction area on NCCT images and T2-weighted MRI.Angina is defined as a transient chest pain or pressure (duration of symptoms < 30 min) caused by insufficient blood flow to the myocardium without significant ST/T changes in ECG and rise of cardiac biomarkers.Myocardial infarction is defined as myocardial necrosis in clinical settings consistent with myocardial ischemia. These conditions can be satisfied by a rise of cardiac biomarkers [preferably cardiac troponin (cTn)] plus at least one of the following: (1) symptoms of cardiovascular ischemia; (2) ECG changes indicative of new ischemia (significant ST/T changes or left bundle branch block); (3) development of pathologic Q waves; (4) imaging evidence of new loss of myocardium or new regional wall motion abnormalities; (5) angiography or autopsy evidence of intracoronary thrombus.

Secondary outcomes are: 1. UIA rupture events during 24-month follow-up; 2. UIA growth events during 24-month follow-up; 3. Change in average Wall Enhancement Index (WEI) at baseline and 24th month. WEI is defined as follows:

Two investigators (with work experience of >10 years, who are blind to the clinical and morphological information) measure the WEI value independently using Vessel-MASS software (Leiden University Medical Center). Three slices with significant enhancement observed by post-contrast VW-MRI at baseline and 24 months will be selected. After tracing the lumen and outer boundaries of the aneurysm wall, the contours of the inner lumen and outer wall of aneurysms will be automatically segmented using the software. If the tracking is not satisfactory, the investigators will manually adjust the contour of the inner cavity and the outer wall. Subsequently, the mean signal intensity (SI) will be calculated automatically using the software. The average and maximum value of the mean SI of the corresponding three slices will be used for further analyses.

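### The incidence rate and both Cox analyses are specified for PR, an undefined term that is not a trial outcome, and neither Cox model is named as the primary analysis of UIA instability

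*Protocol article*

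**What the plan says.** **Analysis (Endpoint and outcome evaluation).** Two sentences describe the time-to-event analysis, and both name the same outcome: "The incident rate (IR) of PR and its 95% confidence interval (CI) are calculated", and "The univariate and multivariate Cox regression analyses are performed in PR-related analysis". The results are to be given as hazard ratios with 95% confidence intervals. No covariates are listed for the multivariate model. Other comparisons are covered in general terms: "The differences between groups in continuous variables are compared by performing the student’s t-tests or Wilcoxon rank sum tests". Categorical data get a chi-square or Fisher test, again with no covariates mentioned.

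**Outcomes (Outcomes and relative definitions).** "The primary efficacy outcome is UIA instability, including aneurysm growth, rupture or aneurysm-related symptoms during 24-month follow-up". The safety outcome is ischemic cerebral or cardiac events. The secondary outcomes are rupture, growth and "Change in average Wall Enhancement Index (WEI) at baseline and 24th month". The abstract words the primary outcome differently: "The primary outcome is aneurysm instability within 24 months after appropriate blood pressure lowering therapy, including aneurysm growth and aneurysm rupture".

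**Allocation (Step 2: Randomization and intervention).** Minimisation is 1:1. "Randomization factors are as follows: age at the time of obtaining the informed consent" (60 and over, or under 60), together with sex and aneurysm location in four levels.

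**Subgroups analysis.** These analyses are restricted to the primary efficacy and safety endpoints, with a separate Cox model in each subgroup.

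**The concern.** The only sentences that say how the trial's incidence rate and hazard ratio are obtained attach them to PR. That abbreviation is not expanded, appears in no other part of the article shown, and matches none of the listed outcomes. Followed literally, the plan ties no overall model to UIA instability. It also lists a univariate and a multivariate Cox model without saying which one decides the trial. In an open-label trial, a choice between two models that is left open until the data are seen is a choice that can follow the result.

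A second, smaller matter is efficiency. Allocation is balanced on three factors, but none of the tests stated without covariates uses them. WEI is defined as a change from baseline, and the article mentions no adjustment for the baseline value.

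**Working it through.** **1. Which outcome could PR be?** The article defines five outcomes: UIA instability, ischemic events, rupture, growth and WEI change. WEI is continuous, so a Cox model could apply to the other four. PR abbreviates none of them, so the intended outcome cannot be read off the text with certainty. The Subgroups analysis section makes UIA instability the likely meaning, but does not state it for the overall comparison. Writing in UIA instability is still not enough: the Outcomes section counts growth, rupture and aneurysm-related symptoms, while the abstract names only growth and rupture.

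**2. The plan's own sample size.** Inputs from the Sample size section: control risk 20.7%, a 50% reduction (to 10.35%), α = 0.05, and 0.90, which is printed as β and read here as power. Two-sidedness comes from Endpoint and outcome evaluation. With unpooled variances:

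- n per arm = (0.207 × 0.793 + 0.1035 × 0.8965) × (1.960 + 1.2816)² / 0.1035² = 0.2569 × 10.507 / 0.01071 = 252.0, taken up to 253.
- After 10% dropout: 253 / 0.9 = 281.1, taken up to 282.

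Both printed figures are reproduced, so the trial is sized on two proportions.

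**3. Does naming a Cox model change the size?** Under proportional hazards:

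- HR = ln(0.8965) / ln(0.793) = 0.471, so ln HR = −0.753.
- Schoenfeld: 4 × 10.507 / 0.753² = 74.1, i.e. 75 events. At an event total of 0.207 + 0.1035 = 0.3105 per pair of patients, that is 242 per arm.
- Freedman: 10.507 × (1.471 / 0.529)² = 81.2, i.e. 82 events, or 265 per arm.
- Expected events with 253 per arm: 253 × 0.3105 = 78.6, about 79. Schoenfeld power: √79 / 2 × 0.753 − 1.960 = 1.386, i.e. about 92%.

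The planned number sits between the two formulas.

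**4. Cost of leaving out the minimisation factors.** The article gives no prognostic strength for age, sex or location, so this is assumed and shown as a range. Both sets of simulations use 506 patients, biased-coin minimisation (0.8) and a logistic model.

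*Set A* (control risk 11.5%, treatment odds ratio 0.47, 2,500 trials):

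| Factor odds ratio | Power unadjusted | Power adjusted |
|---|---|---|
| 1.5 | 64.7% | 65.6% |
| 2.0 | 65.9% | 67.2% |
| 2.5 | 68.3% | 70.6% |

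*Set B* (control risk about 17–20%, treatment log odds ratio −0.7, 2,000 trials; age and sex log odds ratios 0.5, 1.0 and 1.5, i.e. odds ratios of about 1.6, 2.7 and 4.5, with location effects scaled likewise):

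| Strength | Type I unadjusted | Type I adjusted | Power unadjusted | Power adjusted |
|---|---|---|---|---|
| 0.5 | 4.3% | 4.5% | 71.5% | 72.2% |
| 1.0 | 4.1% | 5.5% | 72.1% | 76.4% |
| 1.5 | 2.6% | 4.6% | 70.9% | 79.5% |

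The gains run from 0.7 to 8.6 points. The Monte Carlo standard error of one power estimate is about √(0.72 × 0.28 / 2000) = 1.0 point, so the smallest gains show little by themselves. For type I error it is √(0.05 × 0.95 / 2000) = 0.5 point. The unadjusted test is therefore clearly conservative at the strongest setting and only suggestively so at the other two. In no setting is the unadjusted test's error rate above 5%.

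**5. WEI.** With equal variances σ² and baseline-to-24-month correlation r, the variance of a change score is 2σ²(1 − r), and the residual variance in ANCOVA is σ²(1 − r²). The ratio is (1 + r)/2. For assumed r = 0.3, 0.5 and 0.7 it is 0.65, 0.75 and 0.85. This equals 1/0.65, 1/0.75 and 1/0.85 times the patients, i.e. 54%, 33% and 18% more.

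**The case against.** The strongest reply is that PR is a drafting slip in a condensed article. The Subgroups analysis section shows that Cox is meant for the primary endpoint, and a covariate list is ordinarily left to an analysis plan. Much of this is right, and it rules out several stronger readings:

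- *That the plan ignores the minimisation factors throughout.* This is true of the t-test, Wilcoxon, chi-square and Fisher tests and the univariate Cox model. The multivariate model names no covariates and may include all three factors.
- *That UIA instability will be tested by chi-square, giving three competing p-values.* The sentence on categorical variables is general and names no endpoint. The two-proportion sample size is compatible with such a test, but does not prescribe it. The open choice shown by the text is between two Cox models.
- *That the unadjusted tests are invalid.* After minimisation they tend to be conservative. A t-test on change in a randomised trial is also unbiased, only less precise.
- *That the WEI point weakens the primary analysis.* WEI is a secondary outcome and has no bearing on it.

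The simulations can also be criticised. Neither set uses the 20.7% versus 10.35% design basis, and both use a logistic model although a Cox model is recommended. They show direction and rough scale only.

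What the reply does not remove is the wrong term. An analysis plan can supply missing detail, but the published sentence still assigns the hazard ratio to something that the trial does not measure.

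**Conclusion.** The point holds in a limited form. The article specifies the incidence rate and both Cox models for an outcome that the trial does not have, so the overall analysis of UIA instability is not stated correctly, and no Cox model is designated as primary. This rests on the text alone and needs no assumption.

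The efficiency part is an improvement to make, not an error that biases the trial. Adjusting for the minimisation factors is worth about 1 to 9 percentage points of power. The upper end requires age and sex odds ratios of about 4.5, and the lower end is within simulation noise. ANCOVA for WEI has 65% to 85% of the change-score variance, assuming equal variances and a correlation between 0.3 and 0.7. The sample size stands: about 79 events are expected with 253 per arm, against 75 (Schoenfeld) or 82 (Freedman) for 90% power under proportional hazards.

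**What to change.** 1. Reconcile the abstract with Outcomes and relative definitions on whether aneurysm-related symptoms are part of UIA instability.
2. Replace PR with UIA instability, so defined, in both sentences under Endpoint and outcome evaluation.
3. Name one primary analysis: a Cox model for time from randomisation to UIA instability, with arm adjusted for age (60 and over, or under 60), sex and aneurysm location (four levels), reported as a hazard ratio with 95% confidence interval. Label the unadjusted Cox model and any chi-square test as supportive.
4. For WEI, compare arms by ANCOVA of the 24-month value on the baseline value.

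The cost is wording only. The three factors are known at randomisation, vessel-wall MRI is already scheduled at screening and at 24 months, and no patients need to be added.
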